### Blood samples

 Up to 80 ml of blood will be drawn during the baseline and 18 month visits. These collections will occur as far as is practicable in the morning (between 9 am and 11 am) with the participant in a fasted state. Blood samples will be examined with a detailed immunophenotyping protocol which uses multi-parameter mass cytometry—a powerful technology for the analysis of population dynamics, cellular phenotype and function in the immune system at the single cell level.^73^ A comprehensive panel of antibodies tagged with heavy metal ions will be used to identify phenotypic and functional cell surface markers^73^ in whole blood on the day of sample collection. Samples prepared for mass cytometry will then be frozen and thawed prior to acquisition in batches on a mass cytometer, according to our previously published methods.^78^ This process systematically evaluates the unique repertoires of cell subsets and activation markers to provide a detailed map of an individual’s immune landscape. Following cleaning and quality control of the data, bioinformatic approaches that hierarchically cluster and quantify phenotypically similar cells will be applied for the analysis pipeline.^79^ In a subgroup of participants, fresh blood will be used for stimulation studies to investigate protein and metabolite production by cells belonging to different disease groups following immune challenge.^80^ Routine laboratory bloods will be undertaken to check clotting factors for safety and eligibility for CSF collection via an optional lumbar puncture. PBMCs will be collected and stored in liquid nitrogen for future validation assays. The remaining blood will be centrifuged to produce serum and plasma samples to be stored at −80°C for further testing of inflammatory and neurodegenerative markers in the future, while remaining cells will be stored for future genetic and transcriptional analyses.

### CSF samples

 The optional collection of CSF is expected to be consented to by approximately 20–25% of participants. Upon receiving informed consent, up to 20 ml of participant CSF will be collected through a lumbar puncture. If CSF collection is being obtained as part of the NHS diagnostics, and people are eligible for and consent to take part in this study, to avoid the need for a second lumbar puncture, up to 10 ml of CSF will be collected and stored for research purposes at the time of the NHS lumbar puncture. The lumbar puncture is optional, and participants will be provided with detailed written information on the procedure. All participants will discuss the procedure with a clinician who will perform an individual safety assessment. The safety of lumbar punctures in this population is well documented,^81^ with headache as the most common adverse event (occurring after 0.9–9% procedures, with more than 80% requiring no treatment). Serious adverse events such as infection or bleeding occurring in less than 1/10 000 procedures. The analysis protocols regarding immunophenotyping of blood samples mentioned above will be repeated with the CSF samples. Remaining CSF will also be analysed for biomarkers of infection, inflammation and neurodegeneration, which may provide information about the presence or absence of disease or relate to disease prognosis or severity. Collecting multiple samples from the same participants (ie, blood and CSF) will significantly enrich the study due to the multimodal data, allowing for a more complete profile of immune changes involved in people with cognitive impairment. For example, a key scientific question is the relationship between peripheral and central inflammation, and by collecting paired blood and CSF in a subset of participants, we will be able to contribute to this important area.

### Saliva samples

 In a subgroup of participants, saliva will be collected in a resting, unstimulated state by the participant drooling into a 50 mL collection vial with the head tilted forward, allowing the saliva to accumulate in the mouth. 5–20 mL will be collected within a 10-min time frame following a 1 hour period of not eating or drinking. Following processing, saliva samples will undergo a number of advanced analytical procedures to identify markers of inflammation, τ, phosphorylated-tau, Aβ and α-synuclein.

### Urine samples

 During study visits, 20–30 mL of mid-stream urine will be collected in sterile containers and will also be assessed for markers of inflammation, infection and degenerative changes. Following analysis protocols, remaining urine samples will be stored for future analysis.

### Analysis

 The authors have an extensive background of completing and analysing data from longitudinal research studies in these and similar populations. For example, the NIMROD study^82^ consisted of deep phenotyping and neuroimaging with longitudinal cognitive assessments, exploring the role of brain inflammation in dementia.^83 84^ The aim of this study is to detect differences in immune profiles between cohorts. The continuous variable of cognitive decline, as measured by the battery of neuropsychological assessments, as well as the binary progression to dementia from MCI, is also the outcome of interest. Multivariate statistical techniques alongside high-dimensional clustering, annotation and differential analysis^85^ will be employed to analyse immune cell counts and clinical measures in order to identify key combinations of immune cell clusters that are predictive of disease phenotype and rate of decline.^86^ This procedure will also reduce the dimensionality of the data. Alongside this, standard automated and/or manual gating, followed by parametric/non-parametric tests, will be applied, depending on the distribution of the data sets. Markers of inflammation, τ, phosphorylated-tau, Aβ and α-synuclein from bio-samples, will be compared using standard parametric methods. Cognitive and biomarker data will also be compared between healthy control, MCI-DLB/mild DLB and MCI-AD/mild AD groups in order to identify any group-level differences. Neuropsychological test scores will be converted to domain z scores for correlational analysis with biomarker and clinical data. Repeat measures from follow-up assessments will be normalised to control scores at baseline and change scores correlated with baseline changes to determine predictors of decline. If multiple predictors of decline are identified, regression and other multi-variate statistical methods including mixed effects models will be used to determine the key predictors. Genetic analysis will be used for confirmatory genetics of alleles known to be associated with inflammation or neurodegeneration and for exploratory analyses within collaborative studies.

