### Participants, recruitment and selection

 For early DLB and early AD groups, participants are to be recruited from cognitive disorder clinics in neurology, old age psychiatry and other related services at Cambridge University Hospital (CUH), Cambridge and Peterborough NHS Foundation Trust and Imperial College Healthcare NHS Trust. We will also seek referrals from other linked sites and recruit from the ‘Join dementia research’ (JDR) platform,^76^ where participants are able to travel to CUH or Imperial College Healthcare NHS Trust for biosampling. Control participants will be recruited from healthy older adults who express a willingness to participate in research via locally held research registers and JDR, as well as healthy friends and non-blood-related family members of patient participants who also indicate a willingness to participate.

 Potential participants will be provided with a copy of the participant information sheet and, following a period to consider these materials, will be contacted to ensure eligibility and suitability to partake in the study. An appointment will then be arranged for those willing and suitable to participate either for them to attend the study premises or to receive a home visit from a member of the research team to provide an opportunity to ask further questions and to obtain formal written consent from the participant. Consent for participation in the study and the sharing of pseudonymised data and samples will be taken. Due to the vulnerable nature of the study population and the longitudinal nature of the study, capacity to consent and participate will be considered throughout the study course. Clinicians and researchers recruiting to this study are trained in the assessment of capacity and capacity assessments will take place at each study visit. A potential consultee will be identified at the baseline research visit, and if a participant loses capacity during the study, the consultee process will be followed. Reimbursement for travel and meals will be provided for all study visits.

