### Power calculation

Our aim is for the study to have 80% power to detect differences in proportions of immune cell populations between groups at an alpha of 0.05. For an analysis of covariance with three groups and two covariates (age and sex), a sample size of 90 (30 in each group) would give sufficient power to detect an effect size of 0.33 (Cohen’s f, equivalent to Cohen’s d ~0.35). A sample size of 180 (60 in each group) would detect an effect size of 0.23 (Cohen’s f, equivalent to Cohen’s d ~0.24). By using data from previously published work performed by this group, which investigated myeloid cell subsets using flow cytometry in the NIMROD cohort,^87^ we estimated the effect sizes for significant immune cell differences between DLB, AD and controls to be between Cohen’s D 0.5–0.8. This suggests that sample sizes above 30 per group would be sufficient to detect these differences, with larger sample sizes detecting more subtle differences.

For correlations with cognition, Gate *et al*^75^ identified with mass cytometry immune cell populations in AD correlating with cognitive scores with slopes of magnitude ~0.5. A similar magnitude of correlations (r = 0.37–0.64) has been shown with immune cell subsets detected by mass cytometry and cognitive decline in AD.^88^ To detect correlations of this magnitude would require a sample size of 29 in each group (80% power at alpha = 0.05). A sample size of 60 in each group would detect the more modest correlations ~0.35 (all power calculations performed in G*Power v3.9.7.1).

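### The study is sized on an ANCOVA adjusted for age and sex, but the Analysis section names no covariates for the group comparison and allows rank tests that would drop the adjustment

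*Protocol article*

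**What the plan says.** **Sizing (Protocol article, Power calculation).** The stated target is "80% power to detect differences in proportions of immune cell populations between groups at an alpha of 0.05". The model is given: "For an analysis of covariance with three groups and two covariates (age and sex"), with 90 participants (30 per group) for Cohen's f = 0.33 and 180 (60 per group) for f = 0.23.

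**Group comparison (Protocol article, Analysis).** Three routes are described.
- Multivariate methods with clustering and differential analysis. Covariates are neither named nor excluded.
- Gated populations: "standard automated and/or manual gating, followed by parametric/non-parametric tests, will be applied, depending on the distribution of the data sets".
- Other markers: "Markers of inflammation, τ, phosphorylated-tau, Aβ and α-synuclein from bio-samples, will be compared using standard parametric methods".

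ANCOVA, age and sex do not appear in that section. Regression and mixed models are mentioned only for sorting out predictors of decline, and only if several are found.

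**Who is compared.** Research questions describes the controls as similar in age to the patients. Inclusion criteria admit both sexes above 50 years. The article states no matching rule and says nothing about sex balance between cohorts.

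**The concern.** The article states both a sizing model and a rule for choosing the test, and the two do not fit together. The parametric branch of the rule could be read as the ANCOVA. The non-parametric branch cannot easily be read that way, because the usual rank tests (Mann-Whitney, Kruskal-Wallis) take no covariates. Cell proportions are bounded and often skewed, so that branch may be used often. Whether a population is adjusted for age and sex would then depend on the shape of its distribution, and adjusted and unadjusted results could sit side by side in one report.

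In a non-randomised comparison this matters. Any residual difference in age or sex between cohorts passes into an unadjusted comparison in proportion to how strongly the cell population depends on that variable. It could then be reported as an immune signature of early AD or DLB. By putting age and sex in the sizing model, the authors themselves treated them as the relevant covariates.

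**Working it through.** **1. The plan's own figure.** Inputs from Power calculation: 3 groups, 2 covariates, alpha 0.05, 80% power. For a fixed-effects ANCOVA, df1 = 2, df2 = N − 3 − 2 and noncentrality = f² × N.
- N = 90, f = 0.33: df2 = 85, noncentrality = 0.1089 × 90 = 9.80, power 79.2%.
- N = 180, f = 0.23: df2 = 175, noncentrality = 0.0529 × 180 = 9.52, power 78.8%.
- The f detectable with exactly 80% power is 0.333 and 0.233, so the stated 0.33 and 0.23 are reproduced after rounding.

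**2. Does the sample size depend on the covariates?** Without them df2 = N − 3 (87 and 177), and the detectable f is again 0.333 and 0.233. The sample size figures stand either way.

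**3. Power if the covariates are dropped (assumption).** Suppose f refers to the covariate-adjusted SD, and age and sex explain a share R² of the within-group variance. The unadjusted effect is then f × √(1 − R²).

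| Assumed R² | Power, N = 90 | Power, N = 180 |
|---|---|---|
| 5% | 77.0% | 76.5% |
| 10% | 74.6% | 74.1% |
| 20% | 69.2% | 68.7% |

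**4. False positives from a sex imbalance (assumption).** Two groups of 60, no disease effect, and a marker that differs by b = 0.5 within-sex SD between the sexes. The proportions of one sex in the two groups are p₁ and p₂ = 1 − p₁.
- Bias = b × (p₁ − p₂).
- Estimated standard error = √{2 × [1 + b² p₁(1 − p₁)] / 60}. The true sampling SD with the sex mix held fixed is √(2/60) = 0.1826.
- Rejection probability = Φ[−(1.96 SE − bias)/0.1826] + Φ[−(1.96 SE + bias)/0.1826].

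| Sex mix | Bias (SD) | SE | Two tail terms | Unadjusted type I error |
|---|---|---|---|---|
| 55:45 vs 45:55 | 0.05 | 0.1881 | 0.040 + 0.011 | about 5% |
| 60:40 vs 40:60 | 0.10 | 0.1880 | 0.071 + 0.005 | about 8% |
| 65:35 vs 35:65 | 0.15 | 0.1877 | 0.116 + 0.002 | about 12% |
| 70:30 vs 30:70 | 0.20 | 0.1873 | 0.180 + 0.001 | about 18% |

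Simulation (6,000 replicates) gives 11.2% and 18.2% for the last two rows, and 5.1% and 4.8% with sex in the model. A simulated Mann-Whitney test on the 65:35 case also rejects about 11% of the time, so a rank test gives no protection. With two or three groups, and a fixed or random sex mix, the ranges are 10.7% to 12.5% and 16.2% to 19.3% unadjusted, and 4.8% to 5.2% adjusted.

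**5. The same mechanism for age (assumption).** Suppose both patient groups are older than controls by d SD and the age-cell correlation is r. The spurious effect is f = r × d × √2 / 3. At 60 per group with r = 0.3:
- d = 0.3 gives f = 0.042 and a false-positive rate of about 7%.
- d = 0.5 gives f = 0.071 and about 12%.

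With age in the model the simulated rate is about 5% in both cases.

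**The case against.** The strongest reply is that the plan never says its tests are unadjusted. ANCOVA is a parametric method, so the parametric branch may be exactly the model in Power calculation. That section names the covariates and the target, and the two sections can be read together. The differential analysis listed first in the Analysis section may also take covariates, which cannot be seen from the article. This stands. A reader might infer that the study plans unadjusted comparisons, or that the powered analysis will not be run, and the text proves neither. What remains is narrower: no covariate is named for any group comparison, and the test-selection rule includes a branch in which standard tests cannot adjust.

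The reply is also right on four further points.
- The sample size does not depend on the covariates.
- Controls of similar age lessen the age concern, so the age figures should not be pushed to large differences.
- A reader might add site and batch, since samples are "frozen and thawed prior to acquisition in batches on a mass cytometer". The sizing ANCOVA has neither term, so nothing is dropped between the two sections. Batch handling may lie in the cited methods, the quality control step or a fuller plan.
- A reader might argue that controls drawn from "healthy friends and non-blood-related family members of patient participants" mirror the patients' sex mix through partners. The article does not mention partners and lists research registers and a national volunteer platform as well. The 65:35 versus 35:65 mix is therefore an illustration towards the severe end and is not a forecast.

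**Conclusion.** The point holds in limited form. The sizing section assumes adjustment for age and sex. The Analysis section names none, and for skewed data it permits a test that would remove it. In this non-randomised comparison, following the rule as written can give confounded results that differ from the powered model.

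The size is conditional throughout. With a 0.5 SD sex effect and 60 per group, type I error ranges from about 5% (55:45 versus 45:55) through about 8% (60:40 versus 40:60) to about 11% (65:35 versus 35:65), against about 5% with adjustment. The article gives neither the imbalance nor the sex or age effects, so none of these figures predicts what this study will find. The sample size calculation is not in question.

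**What to change.** In the Analysis section, state that the main between-group comparison of gated populations, clusters and soluble markers is the age- and sex-adjusted model used in Power calculation. When a variable is non-normal, keep the covariates and change the scale: transform the outcome, or fit the same model to its ranks (rank-based ANCOVA). Report unadjusted parametric or rank tests as descriptive only.

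The cost is a sentence or two of wording and two error degrees of freedom (85 instead of 87 at N = 90). No participants or extra data are needed: age bears on eligibility, and demographic information is already collected at the initial assessment. Ethics and dissemination says the full analyses follow the end of the study, so the change can still be made in advance.

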With distinct pathologies, it is possible that AD, DLB and other neurodegenerative diseases have specific peripheral immune profiles. Indeed, in CSF, IL-8 has been found to be higher in AD than in controls, with no difference seen between controls and DLB.^55^ Moreover, in AD, CSF concentration of YKL40 is increased^57^ but is not elevated in people with DLB or MCI-LB compared with controls,^58^ while soluble TREM2 and progranulin were not elevated in DLB unless AD pathology co-existed in these individuals.^58^ A confounder is the dynamic nature of the immune system along the disease trajectory. For example, King and colleagues demonstrated that participants with MCI-LB or MCI-AD had significantly higher plasma levels of IL-1β, IL-2, IL-4 and IL-10, as well as lower concentrations of TNF-α than the control, DLB and AD dementia groups.^59^ In addition, a longitudinal decline in IL-1β, IL-2, IL-4, IL-10 and INF-γ in the same cohort of participants was associated with worsening of cognitive performance.^60^ Although few longitudinal studies exist, these observed changes associated with disease progression in both pro- and anti-inflammatory markers over time complicate the ability to understand the underlying disease mechanisms and, hence, the utility of the cytokines as accurate biomarkers.

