Flow cytometry-based immunophenotyping of cytokine-producing white blood cells in AD, DLB and their prodromal counterparts is another popular way of characterising differences in the immune system that are associated with disease metrics. Cross-sectional studies characterising patient-derived peripheral blood mononuclear cells (PBMCs) have yielded a much richer profile of immune system changes during diseased states. Most previous research has focused on flow cytometry-based characterisation in the context of AD only. For example, work in AD has shown CD8+T cells^61 62^ and CD4+CD28 memory T cells^63^ CD11b+ neutrophils^64^ are increased, while CD4+CD28+CD27+ naïve T cells are reduced^63^ in comparison to controls. However, Amin and colleagues found that people with DLB exhibit reduced proportions of CD4+helper T cells and CD19+HLA-DR+ activated B cells in comparison with people with AD, further highlighting variation between AD and DLB.^50^ Individuals with MCI also exhibit an increased concentration of CD4+T cells compared with control participants.^61^ Circulating myeloid dendritic cells are depleted in AD compared with control and MCI participants, though MCI subjects who later convert to AD exhibit a significant decline in myeloid dendritic cells in parallel with conversion to dementia.^65^ Furthermore, higher concentrations of CD56+ CD3+ natural killer T cells^66^ are associated with a greater disease severity and a poorer cognitive performance on testing, while activated CD8+T-cell levels correlate with parahippocampal microstructural tissue damage, measured with diffusion tensor imaging.^61^ Interestingly, greater CD4+regulatory T-cell (Treg)^67^ and overall CD3+T-cell^66^ numbers independently demonstrate a positive correlation with performance on the mini-mental state examination (MMSE), signifying better performance. The positive association between Treg levels and cognition is highlighted by the higher proportion of Tregs seen in people with MCI compared with those with AD,^67^ further highlighting fluctuations in the immune system across disease progression. Moreover, in Aβ-positive MCI participants, increased circulating levels of myeloid and dendritic cells were increased compared with Aβ-negative, cognitively normal participants, whereas CD3+T cells were increased in Aβ-positive participants regardless of cognitive status.^68^ Due to technical challenges, very few studies have explored neutrophils in AD/DLB, with a study in AD finding increased CD11b+ neutrophils,^64^ which are associated with disease severity. Although greater clarification is required, the evaluation of peripheral immune cells could help distinguish between neurodegenerative diseases, such as AD and DLB and their prodromal forms,^63 67 69 70^ which will increase diagnostic accuracy and prove useful for disease staging.^66 71 72^

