### Research questions

The main aim of this study is to perform deep immunoprofiling of immune changes in early AD and DLB compared with similarly aged healthy controls. The specific research questions are as follows:

Can differences in immunoprofiles in the blood and CSF be identified between participants with early AD and early DLB (which we define as including both prodromal and mild dementia) and similarly aged healthy control participants?Are there longitudinal changes in these immune biomarkers over time, and how are these changes related to clinical features and disease progression?

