### Cohorts

 Participants will be recruited into three separate cohorts. The recruitment target detailed for each cohort allows for a 20% attrition rate over the course of the study. These cohorts will be:

Healthy control participants, defined as participants with MMSE scores of >26 and with the absence of any regular memory complaints/symptoms or any signs or symptoms suggestive of dementia.Participants with early DLB include:Those who meet research criteria for the diagnosis of MCI-LB.^14^Those who meet criteria for mild DLB (CDR score of 0.5 or 1).^5^Participants with early AD include:Those who meet diagnostic criteria for MCI-AD.^13^Those who meet diagnostic criteria for mild AD dementia (CDR score 0.5 or 1).^6^

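### The AD-versus-DLB comparison pools MCI with mild dementia and states no stage adjustment, so unequal MCI shares would enter it as a disease difference; MCI-only signals are diluted against controls

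*Protocol article*

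**What the plan says.** The Research questions section pools the stages by definition: "early DLB (which we define as including both prodromal and mild dementia", and likewise for AD. Under Cohorts, "Participants will be recruited into three separate cohorts": controls, early DLB and early AD. MCI and mild dementia both sit inside each disease cohort, and no target or quota is given for either stage. The Analysis section carries the pooling into the comparison, with data "compared between healthy control, MCI-DLB/mild DLB and MCI-AD/mild AD groups in order to identify any group-level differences".

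The Power calculation aims for "80% power to detect differences in proportions of immune cell populations between groups at an alpha of 0.05" and names the model: "For an analysis of covariance with three groups and two covariates (age and sex), a sample size of 90 (30 in each group", and so on. Stage is not among the covariates. In the Analysis section, MCI stands apart from dementia only as the starting state for the progression outcome.

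The Background describes the immune system's change over the disease course as a confounder. Its example is that "participants with MCI-LB or MCI-AD had significantly higher plasma levels of IL-1β, IL-2, IL-4 and IL-10", with lower TNF-α, than the control, DLB and AD dementia groups. It also cites the "higher proportion of Tregs seen in people with MCI compared with those with AD".

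**The concern.** If a marker depends on stage, the mean of a pooled cohort depends on how many of its members have MCI. Two problems follow.

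- **AD versus DLB.** If the MCI share differs between the cohorts, part of the stage effect appears as a disease effect. Participants come from neurology, old age psychiatry, other linked services and a volunteer platform, and nothing stated keeps the shares equal.
- **Patients versus controls.** A marker altered in MCI but not in dementia, which is the cytokine pattern the Background describes, is averaged with unaffected cases and becomes harder to detect.

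At stake is the disease-specific part of research question 1: whether a difference between early AD and early DLB reflects the disease or the stage at which each was recruited.

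**Working it through.** **Inputs from the protocol article.** 30 or 60 per group, alpha 0.05, three groups, covariates age and sex (Power calculation). The same section expects effects of d 0.5 to 0.8 between DLB, AD and controls. I borrow that range for stage effects, which is an assumption. MCI shares are not given, so a range is shown. Outcomes are normal with unit SD within stage, and tests are two-sided.

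**1. The plan's own figures.** F test with df1 = 2, df2 = N − 3 − 2 and noncentrality f²N.
- N = 90, f = 0.33: 0.33² × 90 = 9.80, power 79.2%.
- N = 180, f = 0.23: 0.23² × 180 = 9.52, power 78.8%.

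The stated figures reproduce. They treat each pooled cohort as having a single mean.

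**2. AD versus DLB with no disease difference.** Let g be the stage gap in SD, and p1 and p2 the MCI shares. The bias is (p1 − p2)g. The variance is 1 + g²[p1(1 − p1) + p2(1 − p2)]/2. With d = bias/SD, the t test has noncentrality d√(n/2).

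Example: g = 0.8, shares 70 and 30%, n = 60. Bias = 0.4 × 0.8 = 0.32. Variance = 1 + 0.64 × 0.21 = 1.134, so SD = 1.065 and d = 0.300. Noncentrality = 0.300 × √30 = 1.65, and the test rejects 37% of the time.

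| MCI shares | Gap (SD) | Bias (SD) | n = 30 | n = 60 |
|---|---|---|---|---|
| 50 v 50% | 0.5 or 0.8 | 0 | 5% | 5% |
| 60 v 40% | 0.5 | 0.10 | 7% | 8% |
| 60 v 40% | 0.8 | 0.16 | 9% | 13% |
| 70 v 30% | 0.5 | 0.20 | 12% | 19% |
| 70 v 30% | 0.8 | 0.32 | 21% | 37% |

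A simulation with the stage counts held fixed (40,000 replicates) gives slightly lower values: 6 to 11% at 60 v 40% and 11 to 36% at 70 v 30%. A linear model with a stage term rejects 4.8 to 5.1% of the time in every case.

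**3. Cohort versus control, marker raised in MCI only, 1:1 mix.** At 0.8 SD the pooled mean shift is 0.5 × 0.8 = 0.40. The average variance is (1 + 1 + 0.25 × 0.64)/2 = 1.08, so d = 0.40/1.039 = 0.385. For the control/MCI/dementia F test (df 2 and 2n − 3) the grand mean is 0.2, and the noncentrality is n(0.2²) + (n/2)(0.6²) + (n/2)(0.2²) = 0.24n.

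| Shift in MCI | n per group | Pooled test | Control/MCI/dementia test |
|---|---|---|---|
| 0.8 SD | 30 | 31% | 64% |
| 0.8 SD | 60 | 55% | 93% |
| 0.5 SD | 30 | 16% | 29% |
| 0.5 SD | 60 | 27% | 54% |

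The pooled figure depends on the mix. At 0.8 SD and 60 per group it is 24% with a 30% MCI share and 84% with a 70% share.

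**4. When pooling is better.** If both stages shift by 0.5 SD, the stage test's noncentrality is 0.125n = 7.5 at n = 60. Its power is 68%, against 78% for the pooled test.

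**The case against.** **Pooling is the declared population.** Research question 1 asks about early disease, defined to include both stages, and a stage-averaged contrast with controls answers it. This stands: the pooled contrast should remain.

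**The covariates appear only in the power calculation**, the pooled comparison is one of several analyses listed, and the Abstract's list of four patient groups could be read as keeping the stages apart. An unseen plan may add stage. This limits the point but does not remove it, because the article states the pooled comparison and names a covariate set without stage.

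**Timing belongs to the longitudinal analyses.** Repeat sampling and MCI progression are planned and bear on research question 2. True, but they do not correct the baseline AD-versus-DLB contrast.

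**Three stronger readings are tempting and not supported.**
- *Opposite stage effects that cancel.* The cytokine findings show a change present in MCI relative to both controls and dementia, which dilutes and does not cancel. The Treg statement has no control comparison. A reversal has to be assembled from separate dendritic-cell studies, one of them comparing Aβ-positive MCI with Aβ-negative cognitively normal people.
- *A demonstrated bias.* The MCI shares are unknown. At equal shares there is none, and at 60 versus 40% it is small.
- *Adjustment for Aβ and phosphorylated tau.* The Background notes that "soluble TREM2 and progranulin were not elevated in DLB unless AD pathology co-existed in these individuals", which might suggest this. That concerns co-pathology, not stage. Adjusting AD versus DLB for these markers conditions on pathology that defines AD and could remove the contrast of interest.

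**Conclusion.** The point holds as a conditional risk and should be dealt with before the data are analysed. As described, the AD-versus-DLB comparison is not protected against unequal stage mix, although the article itself identifies stage as a source of confounding. The false-positive rate runs from 5% at equal MCI shares, through about 6 to 13% at 60 versus 40%, to about 11 to 37% at 70 versus 30%. Those figures assume a stage gap of 0.5 to 0.8 SD and 30 to 60 per group. Separately, an MCI-only signal loses much of its power in the pooled contrast with controls under an assumed 1:1 mix. The documents give neither the shares nor the stage effects. The figures show what the design permits, not what has happened.

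**What to change.** 1. Adjust the AD-versus-DLB contrast for stage (MCI versus mild dementia), which is known at entry because eligibility depends on it. Report the MCI share in each cohort.
2. Keep the pooled cohort-versus-control contrasts as the answer to research question 1.
3. Add, as secondary analyses, stage-specific contrasts with control and the disease-by-stage interaction. Nest stage within the patient cohorts, because it is undefined in controls and a simple additive term would not show stage-specific differences from them.

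**Cost.** The adjustment takes one degree of freedom. With one more covariate, the detectable f stays at 0.333 (N = 90) and 0.233 (N = 180). If the shares differ, the standard error of the adjusted contrast grows by 1/√(1 − (p1 − p2)²) when they average 50%: 1.02 at 60 versus 40% and 1.09 at 70 versus 30%. Stage-specific estimates will be imprecise. At a 1:1 mix there are about 15 per cell at 30 per group and 30 per cell at 60 per group, so an MCI-versus-dementia contrast within one disease has 80% power only for d = 1.06 or 0.74 respectively. The stage test also loses power when both stages shift equally, which is a further reason to keep the pooled contrast.
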